## **5.10 Study visit schedule and procedures**

The participants will undergo a regular assessment every 2 months ( $\pm$  2 weeks)

230 during the first 6 months, followed by assessments every 3 months ( $\pm$  2 weeks)  
231 during the subsequent 18 months. Table 1 shows the visit schedule and study  
232 procedures.

233

234

**Table 1. Study procedures at baseline and each follow-up visit.**

| Items                                                        | Baseline | 2 months | 4 months | 6 months | 9 months | 12 months | 15 months | 18 months | 21 months | 24 months |
|--------------------------------------------------------------|----------|----------|----------|----------|----------|-----------|-----------|-----------|-----------|-----------|
| Inclusion/exclusion criteria assessment                      | √        |          |          |          |          |           |           |           |           |           |
| Informed consent                                             | √        |          |          |          |          |           |           |           |           |           |
| Enrollment and randomization                                 | √        |          |          |          |          |           |           |           |           |           |
| Training and instruction for instillation of eyedrops        | √        |          |          |          |          |           |           |           |           |           |
| Noncycloplegic refraction (Topcon KR-8900; retinoscopy)      | √        | √        | √        | √        | √        | √         | √         | √         | √         | √         |
| Best-corrected distance visual acuity (logMAR, ETDRS charts) | √        | √        | √        | √        | √        | √         | √         | √         | √         | √         |
| Near vision (logMAR, illiterate “E” charts)                  | √        | √        | √        | √        | √        | √         | √         | √         | √         | √         |
| Slit lamp biomicroscopy                                      | √        | √        | √        | √        | √        | √         | √         | √         | √         | √         |
| Non-mydriatic fundus examination (FundusVue)                 | √        | √        | √        | √        | √        | √         | √         | √         | √         | √         |
| Biometry before cycloplegia (Zeiss IOLMaster 700)            | √        | √        | √        | √        | √        | √         | √         | √         | √         | √         |
| Accommodative amplitude (Near point rule)                    | √        | √        | √        | √        | √        | √         | √         | √         | √         | √         |
| Mesopic/photopic pupil size (OPD-Scan III)                   | √        | √        | √        | √        | √        | √         | √         | √         | √         | √         |
| Intraocular pressure (iCare)                                 | √        | √        | √        | √        | √        | √         | √         | √         | √         | √         |
| Corneal endothelial cell density                             | √        |          |          | √        |          | √         |           | √         |           | √         |

|                                                                                          |   |   |   |   |   |   |   |   |   |   |
|------------------------------------------------------------------------------------------|---|---|---|---|---|---|---|---|---|---|
| (Topcon SP-1P)                                                                           |   |   |   |   |   |   |   |   |   |   |
| Distant/Near magnitude of exodeviation                                                   | √ | √ | √ | √ | √ | √ | √ | √ | √ | √ |
| (Prism and alternate cover test)                                                         |   |   |   |   |   |   |   |   |   |   |
| Distant/near exotropia control (Office-based scale)                                      | √ | √ | √ | √ | √ | √ | √ | √ | √ | √ |
| Distant/Near stereoacuity (Random Dots Distant Test; Randot Preschool Stereoacuity test) | √ | √ | √ | √ | √ | √ | √ | √ | √ | √ |
| Near point of convergence (Near point rule)                                              | √ | √ | √ | √ | √ | √ | √ | √ | √ | √ |
| Fusional vergence amplitude (Synoptophore)                                               | √ | √ | √ | √ | √ | √ | √ | √ | √ | √ |
| Accommodative convergence/accommodation (Far gradient method)                            | √ | √ | √ | √ | √ | √ | √ | √ | √ | √ |
| Dominant eye                                                                             | √ | √ | √ | √ | √ | √ | √ | √ | √ | √ |
| Wavefront aberrometry (Tracey iTrace)                                                    | √ | √ | √ | √ | √ | √ | √ | √ | √ | √ |
| Choroidal structural and vascular component (OCT/OCTA, Optovue)                          | √ | √ | √ | √ | √ | √ | √ | √ | √ | √ |
| Cycloplegic refraction (Topcon KR-8900)                                                  | √ |   |   | √ |   | √ |   | √ |   | √ |
| Mydriatic fundus examination (Volk Digital Wide Field Lens)                              | √ |   |   | √ |   | √ |   | √ |   | √ |
| Dispensation of study medication/dosing compliance diary and symptom inquiry             | √ | √ | √ | √ | √ | √ | √ | √ | √ | √ |

|                              |   |   |   |   |   |   |   |   |   |   |
|------------------------------|---|---|---|---|---|---|---|---|---|---|
| Daily activity questionnaire | √ | √ | √ | √ | √ | √ | √ | √ | √ | √ |
|------------------------------|---|---|---|---|---|---|---|---|---|---|

236 **5.11 Clinical examinations**

237 **1) Noncycloplegic refraction**

238 ⑩ Topcon KR-8900 (Topcon Corp, Tokyo, Japan) and manual refraction

239 **2) BCVA**

240 ⑩ ETDRS charts (Good-Lite Company, Illinois, USA)

241 ⑩ 4 meters

242 ⑩ With the manual refraction and trial frames

243 **3) Near vision**

244 ⑩ Illiterate “E” charts (Precision Vision, Sussex Vision Intl. Ltd, West Sussex,  
245 UK)

246 ⑩ 40 cm

247 ⑩ With the manual refraction and trial frames

248 **4) Slit lamp biomicroscopy**

249 ⑩ To evaluate the eyelid, eyelashes, conjunctiva, cornea, anterior chamber,  
250 iris, pupil, lens, and anterior vitreous

251 **5) Non-mydriatic fundus examination**

252 ⑩ FundusVue (Crystalvue Medical Corporation, Taiwan, China)

253 ⑩ To provide color retinal image

254 **6) Biometry before cycloplegia**

255 ⑩ Zeiss IOL Master 700 (Carl Zeiss Meditec Inc, Dublin, CA)

256 ⑩ To obtain ocular parameters, including AL

257 **7) Accommodative amplitude (AA)**

258 ⑩ Near point rule (rod with a moveable target and metric markings)

259 ⑩ Monocularly

260 ⑩ With the manual refraction and trial frames

261 ⑩ The near point of accommodation is determined when the participant  
262 reports that the letters become blurred, and clarity can not be regained,  
263 when the target is moved towards the participant's eyes.

264 **8) Photopic and mesopic pupil size**

265 ⑩ OPD-Scan III (Nidek, Gamagori, Japan)

266 ⑩ Average of at least 5 consecutive measures

267 **9) Intraocular pressure (IOP)**

268 ⑩ ICare rebound tonometer (Icare Finland Oy, Helsinki, Finland)

269 ⑩ Average of 3 IOP values

270 **10) Corneal endothelial cell density**

271 ⑩ Topcon SP-1P (Topcon Corp, Tokyo, Japan)

272 **11) Distant/near magnitude of exodeviation**

273 ⑩ PACT

274 ⑩ Accommodative targets for fixation at distance (6 m) and near (33 cm)

275 ⑩ Measure after 1 hour of monocular occlusion using a patch.

276 **12) Distant and near control**

277 ⑩ IXT office control scale ranging from 0 (phoria, best control) to 5 (constant  
278 exotropia, worst control) at both distance and near fixation.

279 ⑩ Intermittent Exotropia Control Scale:

280 5 = Constant exotropia

281 4 = Exotropia > 50% of the exam before dissociation

282 3 = Exotropia < 50% of the exam before dissociation

283 2 = No exotropia unless dissociated, recovers in > 5 seconds

284 1 = No exotropia unless dissociated, recovers in 1–5 seconds

285 0 = No exotropia unless dissociated, recovers in < 1 second (phoria)

Levels 5 to 3 are assessed during an initial 30-second period of observation. Levels 2 to 0 are graded as the worst of three rapidly successive trials. An occluder is placed over the right eye for 10 seconds and then removed, measuring the length of time it takes for fusion to become re-established. The left eye is then occluded for a 10-second period and the time to re-fusion is similarly measured. A third trial of 10-second occlusion is performed, covering the eye that required the longest time to re-fuse. The worse level of control observed following the 3, 10-second periods of occlusion should be recorded for that visit.

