## **4.2 Secondary objective**

### **4.2.1 Key secondary objective**

To determine the effect of 0.01% atropine eyedrops on exotropia conditions in children with myopia and IXT.

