## **5.8 Study intervention and termination**

All eyedrops (0.01% atropine sulfate, 1% hydroxypropyl methylcellulose) will be prepared in the same single-dose package without preservative, with the same solvent (1% hydroxypropyl methylcellulose). Participants will receive one drop in each eye once per night.

The single-dose containers of eyedrops will be stored in the area only accessible to the investigator who is not masked to treatment. The eyedrops should be stored at room temperature (15-25°C).

Participants and their guardians will be instructed on the administration of eyedrops after recruitment. A 2- or 3-month dosage of eyedrops will be provided at each visit after finishing all the ocular examinations, and all the empty eyedrop containers will be returned at the next visit, to calculate the compliance rate.

The intervention will be discontinued if the guardian or participant requests to withdraw, or participants has severe allergic response, or aggravation of IXT fulfilling the deterioration criteria for two consecutive follow-ups. IXT deterioration criteria will be met by either development of constant exotropia  $\geq 10$  PD at distance and near or presenting with a decrease

in near stereoacuity of at least 2 octaves. When the deterioration criteria are first met, a retest will be performed after a 10-minute break to confirm or refute the result. The participants experiencing deterioration for 2 consecutive follow-ups will be requested to cease the intervention, and then underwent a further two-month observation period. If participants still fulfill the deterioration criteria, surgery will be recommended.

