### **5.9.2 Secondary outcomes**

- 1) Cycloplegic SE change from baseline at 2 years.
- 2) Change from baseline in axial length, monocular function (BCVA, near vision, accommodative amplitude [AA] and photopic/mesopic pupil size), exotropia conditions (distant/near magnitude of exodeviation and distant/near exotropia control), binocular vision (distant/near stereoacuity, near point of convergence [NPC], accommodative convergence/accommodation [AC/A] ratio, and fusional vergence amplitude [FVA]) and safety parameters (intraocular pressure [IOP] and corneal endothelial cell density [ECD]) at 1 year and 2 years.
- 3) Change in choroidal parameters and higher-order aberrations.

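### Exotropia control, one of two measures for the key secondary objective, is a single unreplicated grade per distance per visit with no stated precision; averaging three gradings at the main visits would be a cheap gain.

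*Combined protocol and SAP*

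**What the plan says.** Section 4.2.1 gives the key secondary objective: "To determine the effect of 0.01% atropine eyedrops on exotropia conditions in children with myopia and IXT". Section 5.9.2 defines those conditions by two measures: "exotropia conditions (distant/near magnitude of exodeviation and distant/near exotropia control".

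Section 5.11 item 12 sets the grading rule for control, on a scale of 0 to 5 at distance and at near:

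- Upper levels: "Levels 5 to 3 are assessed during an initial 30-second period of observation".
- Lower levels: "Levels 2 to 0 are graded as the worst of three rapidly successive trials".
- What is kept: "The worse level of control observed following the 3, 10-second periods of occlusion should be recorded for that visit".

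Other items in section 5.11 are averaged within the visit. Item 9 (intraocular pressure) says "Average of 3 IOP values" and item 8 (pupil size) says "Average of at least 5 consecutive measures". Section 5.8 has one same-visit repeat related to exotropia: when the deterioration criteria are first met, "a retest will be performed after a 10-minute break to confirm or refute the result". That repeat serves the decision to stop treatment, not the control outcome.

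Table 1 schedules control at all ten visits. Section 7 plans GEE models for longitudinal change and names no baseline covariate. Section 5.6 sizes the trial for spherical equivalent only. No section gives an SD, a repeatability figure or a power for control.

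**The concern.** Control is intermittent by definition. Levels 0 to 2 apply only when no spontaneous deviation is seen, so one 30-second observation decides which half of the scale a child enters. A child whose condition has not changed can fall on either side of that boundary at two visits. The three occlusion trials do not repeat the 30-second observation, and they keep the worst result instead of averaging.

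The outcome is change from baseline, so in an unadjusted change score the error in the single baseline grade enters every later comparison.

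The introduction says that the influence of atropine on exotropia is unknown, because earlier trials excluded children with strabismus. A non-significant difference in control could therefore be taken as reassurance. If the measure is imprecise, such a result is also likely when some harm exists.

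**Working it through.** **The plan's own figure.** Section 5.6 uses a difference of 0.22 D, SD 0.57 D, 160 and 80 children, two-sided 5%. The standard error factor is √(1/160 + 1/80) = 0.1369. Then 0.22/(0.57 × 0.1369) = 2.82, and 2.82 − 1.96 = 0.86, which gives 80.5% power. Allowing for 20% drop-out, 240/0.8 = 300. Both figures reproduce, but they concern spherical equivalent. Only the 160 and 80 carry over to control.

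**How much one observation can vary.** Assume that 5-second deviations start at random, one per minute. The chance of seeing none in 30 seconds is exp(−35/60) = 56%, so the same child is graded 3 or worse in 44% of windows. If every such window gives level 3, the SD of one grade is the gap between the two levels times √(0.56 × 0.44) = 0.50:

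| Level when no deviation is seen | SD of one grade |
|---|---|
| 2 | 0.50 |
| 1 | 0.99 |
| 0 | 1.49 |

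A separate simulation took level 2 as the lower value, with children deviated 10% to 70% of the time in cycles of 10 to 60 seconds. It gave SDs from about 0.2 to 1.0. The error SD is therefore uncertain; 0.8 is used below as an illustration.

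**Effect on the 1-year comparison.** Assume error SD 0.8 and true-change SD 0.8.

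- SD of change = √(true-change variance + 2 × error variance per visit).
- Detectable difference at 80% power = 2.80 × SD × 0.1369.
- Power for 0.4 levels comes from 0.4/(SD × 0.1369) − 1.96.

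| Control at each of the two visits | Error variance per visit | SD of change | Detectable difference | Power for 0.4 levels |
|---|---|---|---|---|
| One grade | 0.64 | √1.92 = 1.39 | 0.53 | 56% |
| Mean of three, half the error shared within a visit | 0.32 + 0.32/3 = 0.427 | √1.493 = 1.22 | 0.47 | 67% |
| Mean of three, independent errors | 0.64/3 = 0.213 | √1.067 = 1.03 | 0.40 | 81% |

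With one grade, error is 1.28/1.92 = 67% of the variance of an individual child's change. For error SD and true-change SD each between 0.6 and 1.0, the share runs from 42% to 85%. With true-change SD 0.5 to 1.0 and error SD 0.5 to 1.5, it runs from 33% to 95%.

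**Credit for the planned repeated visits.** There are five follow-up visits to 12 months (2, 4, 6, 9 and 12). Suppose the true change is steady over them and the errors are independent between visits.

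- Single grades throughout: variance 0.64 + 0.64 × (1 + 1/5) = 1.408, SD 1.19, detectable difference about 0.45, power 69%.
- Three gradings at baseline and 12 months, independent errors: 0.64 + 0.213 + (4 × 0.64 + 0.213)/25 = 0.964, SD 0.98, power about 85%.
- The same with half the error shared: 0.64 + 0.427 + (4 × 0.64 + 0.427)/25 = 1.186, SD 1.09, power about 77%.

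**Credit for baseline adjustment.** Use the same five visits with single grades, adjusted for the baseline grade. With between-child SD s, the residual variance is s² + 0.64 + 0.128 − s⁴/(s² + 0.64). For s = 0.8 this is 1.088 (power 80%); for s = 1.2 it is 1.211 (power 76%).

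**The case against.** A reader might infer that chance changes in grade swamp the readings, or that the whole grade comes from a 30-second look. The documents support neither. Levels 0 to 2 rest on three occlusion trials. With no repeatability figure given, the assumed error ranges from a minority of the change variance to most of it. Children who never deviate spontaneously, and those who are constantly exotropic at the graded distance, contribute no noise from the 30-second window.

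A reader might also infer a false treatment difference. Under randomisation with masked examiners the error should be similar in both arms. It widens the interval and does not shift the estimate.

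The analysis side of the objection is strong. The all-visit GEE could already give about 69% power, and baseline adjustment 76% to 80%, with no change to the examination. Three limits remain: the GEE figure needs a steady change and estimates an average over follow-up, whereas the named outcomes are change at 1 and 2 years; section 7 does not specify the adjustment; and the 0.4-level target has no source in the documents.

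It is also true that item 12 follows a cited published scale, that averaging instrument readings does not oblige anyone to average an ordinal grade, and that size of deviation serves the same objective. Repeated dissociation may alter later grades, so 81% is a best case. These points make this an improvement, not the correction of an error.

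**Conclusion.** The point holds as one of precision. Control is a named measure for the key secondary objective, it is recorded once per distance per visit, and no precision is stated for it. Under the illustrative SDs, three gradings take power for a 0.4-level difference in 1-year change from 56% to between 67% and 81%. If the five visits are pooled, the move is from about 69% to between 77% and 85%. All of these figures rest on assumed error and true-change SDs. The pooled ones also assume a steady change and independent errors between visits. A smaller error SD would shrink the gain. The trial remains valid without the change, but a non-significant result on control would then be weak evidence of no effect.

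**What to change.** - **Section 5.11 item 12:** at baseline, 12 and 24 months, grade control three times at distance and three times at near. Separate the gradings by tests that do not dissociate the eyes, and complete all of them before the 1-hour patch used for the deviation measurement. Define the control outcome at these visits as the mean of the three grades.
- **Section 7:** adjust the control analysis for the baseline grade. Report the between-group difference with its confidence interval, and state that a non-significant difference will not be presented as no effect.
- **If the visits are already complete:** the section 7 changes still apply, using the all-visit longitudinal model.

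The cost is a few more minutes and extra brief occlusions per child at three visits. At most, two further assessments × two distances × three trials gives 12 more 10-second occlusions per visit. Two more CRF fields per distance are needed, but no new equipment or staff. The repeats may not be fully independent. The section 5.8 criteria are left unchanged.

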### **13) Distant stereoacuity**

- ⑩ Random Dots Distant Test (P/N 1006, Vision assessment Corporation, Illinois, USA)
- ⑩ 3 meters
- ⑩ Ranging from 63 to 400 arcsecs (log stereoacuity values, 1.8 to 2.6 log arcsecs)
- ⑩ Subjects unable to identify shapes at the 400 arcsecs level are recorded as having 'nil' stereo (log stereoacuity value, 3.2 log arcsecs).

### **14) Near stereoacuity**

- ⑩ Randot Preschool Stereoacuity test (Stereo Optical Co., Inc, Illinois, USA)
- ⑩ 40 cm
- ⑩ Testing disparities at 800, 400, 200, 100, 60 and 40 arcsecs
- ⑩ The result is recorded as the smallest disparity at which the subject could correctly identify at least two of the three shapes.

309 ⑩ Participants who are unable to identify the largest disparity (800 arcsecs)  
310 are recorded as having 'nil' stereo (log stereoacuity value, 3.2 log  
311 arcsecs).

## 312 **15) Near point of convergence (NPC)**

313 ⑩ Near point rule

314 ⑩ The target is gradually moved towards the center of the participant's eyes  
315 at a speed of 1 cm/s until the participant reports double vision, or the  
316 examiner notes an outward deviation of one eye.

317 ⑩ The distance from the target to the spectacle plane is recorded as the NPC  
318 distance in centimeters.

## 319 **16) Fusional vergence amplitude (FVA)**

320 ⑩ Synoptophore (Haag Streit UK Ltd, Essex, UK)

321 ⑩ Fusion slides subtending a visual angle of 6 degrees horizontally

322 ⑩ The participants are first told to move the arms of the synoptophore by  
323 themselves to overlap and fuse the images of a butterfly and a cat. The  
324 examiner then slowly abducts or adducts the synoptophore tubes, until 2  
325 distinct images are observed by the participant. The range between the 2  
326 breakpoints

## 327 **17) Accommodative convergence/accommodation (AC/A) ratio**

328 ⑩ Far gradient method

329 ⑩ 6 meters

330 ⑩ Minus lenses (-3.00 D)

331 ⑩ Stimulating a change in accommodation using minus lenses, and dividing  
332 the resulting change in deviation (in PDs) by the change in lens power.

**18) Wavefront aberrometry**

⑩ ITrace (Tracey Technologies, Texas, USA)

**19) Choroidal structural and vascular component**

Optical coherence tomography (OCT) and optical coherence tomography angiography (OCTA) (Optovue, Inc., Fremont, CA)

**20) Cycloplegic autorefraction**

⑩ Topcon KR-8900 (Topcon, Tokyo, Japan)

⑩ Instill 6 drops of 1% tropicamide at a 5-minute interval and measure after another 10-minute rest.

⑩ Further cycloplegic eyedrops should be given if the pupillary light reflex is still present or the pupil size is less than 6.0 mm ten minutes after the last eyedrop.

All the procedures will be performed by trained ophthalmologists and optometrists, who are masked for the treatment assignment.

At baseline, the participant will be prescribed best-corrected spectacles if the ones worn are inappropriate for either a difference of spherical power or cylinder power exceeding 0.25D. Participants will be inquired whether photophobia exists at baseline, because some IXT patients may have the symptom.

Daily outdoor hours and self-report symptoms related to allergy, blurred near vision, photophobia, or any discomfort are inquired at each visit.

During the follow-up, if a participant has non-serious ocular events e.g., bacterial or allergic conjunctivitis, the guardian should contact the investigator and stop using eyedrops under the investigator's guidance. This duration of

stopping treatment should not exceed 4 weeks (28 days).

## **6. Data collection and management**

Before the trial begins, investigators and study coordinators will receive training on trial processes and procedures, including the overview of the trial, consent process, study procedures, ocular evaluation methods, completion of the case report form (CRF), emergency processing and adverse events reporting. The study coordinators will collect all data from trial participants and record it on the paper CRF. Electronic records will be double entered by two investigators separately, and raw data will be checked for inconsistency.

